## Abstract

**Introduction:**

Doctors have a legal requirement and duty of care to ensure patients are enabled to make an informed decision about their treatment, including discussion of the benefits, risks and alternatives to a procedure. A patient-centred approach to consent has been firmly established in Ireland, and fundamental to this is the ability to engage in a dialogue that offers comprehensible information to patients. Telemedicine has revolutionised the way we can deliver care to patients in the modern era of computers, tablets, and smartphones, and its use has been rapidly expanded. Novel digital strategies to improve the informed consent process for surgical procedures have been increasingly under investigation over the last 10–15 years and may offer a low cost, accessible and tailored solution to consent for surgical interventions. Within vascular surgery, superficial venous interventions have been associated with a high number medicolegal claims and also represents an area within the specialty with rapidly evolving technology and techniques. The ability to communicate comprehensible information to patients has never been greater. Thus, the author’s aim is to explore whether it is feasible and acceptable to deliver a digital health education intervention to patients undergoing endovenous thermal ablation (EVTA) to supplement the consent process.

**Methods:**

This is a prospective, single centre, randomised controlled, feasibility trial recruiting patients with chronic venous disease deemed suitable to undergo EVTA. Patients will be randomised to receive either standard consent (SC) or a newly developed digital health education tool (dHET). The primary outcome is feasibility; assessing the recruitment and retention rate of participants and assessing acceptability of the intervention. Secondary outcomes include knowledge retention, anxiety and satisfaction. This feasibility trial is designed to recruit 40 patients, which will allow for a moderate dropout rate. This pilot study will inform the authors of the appropriateness of an adequately powered multicentre trial.

**Discussion:**

To examine the role of a digital consent solution for EVTA. This may improve and standardise the consent dialogue with patients and may have the potential to reduce claims related to poor consent processes and disclosure of risks.

**Ethical committee reference:**

Ethical approval has been sought and received from both the Bon Secours Hospital and RCSI (202109017), on 14 May 2021 and 10 October 2021, respectively.

**Trial registration:**

ClinicalTrials.gov Identifier: NCT05261412, registered on 1 March 2022

**Supplementary Information:**

The online version contains supplementary material available at 10.1186/s40814-023-01336-9.

## Introduction

### Background

Varicose veins (VV) affect one third of the adult population, and chronic venous disease (CVD) has a negative effect on quality of life (QoL), which can be significantly improved by treatment [1–4]. Chronic venous insufficiency (CVI) can be complicated by venous ulceration in over 3% of patients, and chronic treatment with dressings has been estimated to consume 2% of the health budget. Over the last 15 years, minimally invasive endovenous techniques to treat VV have been introduced and are proven to be cost-effective and safe, particularly when performed under a local anaesthetic in an outpatient setting [5]. The American Venous Forum, in 2011, and the National Institute for Health and Care Excellence (NICE), in 2013, have recommended endovenous thermal ablation techniques (EVTA), as the first-line treatments for truncal venous reflux [6, 7].

Doctors have a legal requirement and duty of care to ensure patients are enabled to make an informed decision about their treatment, including discussion of the benefits, risks and alternatives. This is reflected in the Health Service Executive (HSE) National Consent Policy and Irish Medical Council ‘Guide to Professional Conduct and Ethics’ [8]. A patient-centred approach to consent has been firmly established in Ireland since 2000 and reminds us that we have a duty to involve patients in decisions about their treatment of care and to engage in a dialogue that offers comprehensible information. This is in keeping with the fundamental ethical principle of autonomy [8].

Interventions to improve information transfer and comprehension in the consent process, such as providing standard patient information leaflets (PIL), report mixed results [9]. Information leaflets used during the process of consent have been shown to increase patient factual recall and satisfaction with the consent process and are considered best practice [10–16]. However, even well considered PILs, co-designed with patient or client engagement, do not always cover the less common areas of concern or risk which may be material to an individual patient [9]. More rigorous approaches are time and cost intensive, and can adversely impact on the efficiency of healthcare delivery, which limits scalability.

Telemedicine has revolutionised the way we can deliver care to patients in the modern era of computers, tablets and smartphones, and its use has been rapidly expanded [15]. Digital platforms are a novel tool to potentially improve dialogue and communication between doctors and patients. Patients in general have high satisfaction ratings for telemedicine, but certain patient groups may be less likely to engage or benefit from it on account of disability, technological illiteracy or access [15]. Therefore, the use of novel digital technologies for consent may offer a low cost, accessible and tailored solution.

### Rationale for study

Providing patients with understandable information is essential in order to respect and promote patients’ autonomy and protect them from harm. In healthcare settings, informed consent has a specific function to provide an instrument to guarantee a balanced doctor-patient relationship, whereby the patient gives explicit authorisation to accept or refuse treatment offered by the doctor. Novel digital strategies to improve the informed consent process (disclosure of information and its comprehension) for surgical procedures have been increasingly under investigation over the last 10–15 years [17–19]. Recently, a study by Gesualdo et al. reported that digital technologies for informed consent do not negatively affect patients and appear desirable in a surgical setting [20].

Vascular surgery is underrepresented in the aforementioned studies of novel strategies for informed consent, with only one study by Bowers et al. which included four minimally invasive vascular procedures but did not include EVTA [21]. Previous studies have reported that VV procedures were the primary source for medico-legal claims in vascular surgery [22–24] and were involved in 48% of successful claims in one study from the United Kingdom (UK) [24]. Although these studies likely represented mostly open VV surgery, vascular interventions are constantly evolving to become less invasive as technology advances and thus the ability to disclose comprehensible information to patients has never been greater. Improved consent and better communication with patients could significantly reduce the number of future claims. Pre-prepared consent forms to promote standardisation of the consent process could also potentially reduce claims [25].

Thus, we aim to explore whether it is feasible and acceptable to deliver a digital health education intervention to patients undergoing EVTA to supplement the consent process. The rationale for this study is to assess whether conducting a large definitive randomised control trial with this protocol is feasible in a busy day-surgery practice.

## Aims and objectives

### Aim

The authors’ aim to undertake a methodologically robust, single-centre, randomised controlled pilot feasibility trial assessing the feasibility of introducing a digital health education tool (dHET) for VV consent into a busy surgical practice. Our secondary aim is to explore whether the intervention has any impact on patients’ knowledge-recall, satisfaction or anxiety.

### Primary objective

The primary objective is as follows: to determine if the introduction of a digital health education tool for consent is feasible and practical in a busy day surgery practice by examining the number of eligible participants, recruitment rates to the study, retention rates of participants, acceptability of the study, protocol adherence, barriers to delivery of the assigned interventions and the time taken to complete the assigned intervention.

### Secondary objectives

The VVEIN pilot trial also includes secondary objectives related to the potential effect of the digital health education tool on knowledge recall, satisfaction and anxiety. Secondary objectives will be determined by examining the effect of dHET on early knowledge recall, patient satisfaction with the consent process, delayed knowledge recall, anxiety and satisfaction (at 2 weeks), the time spent by patients with the responsible surgeon and the number of questions asked by patients before signing consent.

### PICO

#### Population

The population includes patients with superficial venous incompetence undergoing an EVTA procedure.

#### Intervention

The intervention is as follows: digital health education tool (dHET) (multimedia file with video animation, narration and graphics) for informed consent for EVTA procedures—developed with EIDO^TM^healthcare and delivered on a handheld tablet device.

#### Comparison

Standard consent (verbal discussion + written information leaflet EIDO™ healthcare)

Primary outcomes:Eligible participantsRecruitment numberRetention numberAcceptabilityAdherence to protocolBarriers to assigned interventionTime taken to complete assigned intervention

Secondary outcomes:Early knowledge recallPatient satisfactionPatient anxietyDelayed knowledge recallTime spent with surgeonNumber of questions asked by patient

## Study methods

### Statement of design

The VVEIN study is a two-arm, randomised pilot feasibility trial to assess the practicality of supplementing the consent process for EVTA procedures with a dHET. This randomised feasibility study shall be carried out in accordance with the guidance set out by the Consolidated Standards of Reporting Trials (CONSORT) group for randomised pilot and feasibility trials. http://www.consort-statement.org [26]. The VVEIN study has been prospectively registered on ClinicalTrials.gov. (NCT Identifier: NCT05261412).

Participants shall be randomised in a 1:1 ratio to one of two parallel groups. Study flow is shown in Fig. 1. The dHET was co-designed with EIDO healthcare and contains information about EVTA procedures and the benefits, alternatives and risks of the procedure. EIDO healthcare information is delivered in a multimedia file with video animation, narration and graphics.

**Fig. 1 Fig1:**
[figure not shown]
CONSORT flow diagram for VVEIN pilot feasibility study

### Study flow

The study flow is shown in Fig. 1.

### Participants

For the purpose of this pilot study, two vascular surgeons at the study location will be recruited to participate in the trial. Two were selected for pragmatic reasons in this initial pilot study. All consenting patients attending the vascular outpatient department of the two recruited surgeons, with truncal saphenous vein incompetence, suitable for an EVTA procedure (with or without adjunctive procedures (phlebectomy/foam sclerotherapy)) will be assessed for eligibility. Where both legs are being treated, only the first leg/episode of consent shall be randomised to the study.

#### Inclusion criteria

Deemed suitable for EVTA by treating surgeonFirst procedure for superficial venous incompetenceFull consent > 18 yearsProficient in English

#### Exclusion criteria

Redo or second procedure for superficial venous incompetence (in same or opposite leg)Cognitive impairment or unable to consentNot meeting inclusion criteria

### Expected study duration

Ethical approval was sought and approved in May 2021 from the research ethics committees (REC) at the study location and at the Royal College of Surgeons in Ireland (RCSI). Recruitment will commence in Spring 2022 and continue over a maximum 12-month period until March 2023 or until recruitment targets are met. Subsequent amalgamation of data and analysis will be performed upon completion with the final results expected thereafter.

### Study setting

Patients who meet the inclusion criteria will be identified at the surgical outpatient department at the study location and invited to participate by a member of the research team. An initial consent and information process shall be carried out with patients deemed suitable for EVTA by their responsible surgeon. All patients (agreeable to participate and those unsure) will be provided with a PIL for the study approved by the local REC, for education purposes. Upon re-presentation to the day ward for their procedure, patients will be verbally reconsented for inclusion prior to randomisation and allocation to a study arm.

### Intervention

*Control group*: Participants in the control arm will undergo *Standard Consent (SC)* which will consist of paper PIL provided by EIDO™ healthcare followed by a verbal discussion (standardised by following a checklist of topics to discuss) with the responsible consultant surgeon and signing of their consent form. The time taken to read the PIL (recorded with a stopwatch) will be recorded. The time spent with the responsible surgeon will also be recorded, as will the number of questions asked by the patient.*Intervention*: Participants randomised to the intervention dHET will receive the dHET followed by a verbal discussion (as above) and signing of their consent form. The dHET will be delivered on a tablet computer and facilitated by a research assistant who will ensure all technological issues are overcome but will not engage with the participant with regard facilitating better understanding of the content. The digital offering will be interactive; patients will be able to traverse through each section at their own pace with the ability to re-visit sections as many times as they wish. It also contains a short narrated animation of the procedure, which they can play, rewind or fast forward. The time spent reading each section of the dHET and time spent watching the animation will be recorded. The time spent with the responsible surgeon will also be recorded, as will the number of questions asked by the patient.

All patients will complete a knowledge questionnaire at baseline, post intervention on the day of surgery and at the 2-week follow-up telephone interview. As no validated knowledge questionnaire for EVTA procedures was available, we developed one based on information provided in the EIDO^TM^ PIL and from a separate body of work by our team—expert consensus for essential information for varicose vein surgery—a modified Delphi study [27]. The knowledge questionnaire consists of 20 True or False questions. Patients are encouraged not to guess and to choose ‘Unsure’ if they do not know the answer. The questionnaire was piloted among post-operative EVTA patients and a mean score of 10.39 was achieved.

The six-item State trait Anxiety Inventory (STAI-6) will also be completed at baseline, post intervention on the day of surgery and at the 2-week follow-up telephone interview. The short form of the STAI was developed for use in circumstances when the full form is inappropriate, such as a busy day-surgery ward. It correlates closely with the full-form and has acceptable reliability and validity [28].

The client satisfaction questionnaire (CSQ-8) will be administered on the day of surgery and repeated at the 2-week follow-up telephone interview. The CSQ-8 questionnaire consists of eight self-report questions, constructed with a four-point Likert scale reply. The minimum achievable score is 8, indicating poor satisfaction, and maximum score is 32, indicating a high level of satisfaction. This tool has been found to be acceptable in studies examining patient satisfaction with consenting methods [29–32].

#### Contraindications, cautions and interactions to be considered

There are no contraindications or cautions to be considered when utilising this dHET to supplement the consent process. The information contained in the dHET reflects the HSE National Consent Policy and Irish Medical Council ‘Guide to Professionalism and Ethics’ [8]. No variation in risk to standard consent protocols has been identified.

### Data collection

Baseline patient demographic data will be collected pseudonymously from patients and/or from patient medical records. The following will be recorded:AgeGenderLevel of education (highest achieved)Primary schoolSecondary schoolThird levelHealth literacy—rapid estimate of adult literacy in medicine (revised) REALM-R—score of 6 or less considered to be at risk for poor health literacy [33, 34]

Outcome data will be collected prospectively. Outcome data and definitions are provided below:

Primary outcomes▪ Eligible participantsNumber of eligible participants (meeting inclusion criteria)▪ Recruitment numberNumber of participants consenting to participate▪ Retention rate(Number of patients who consent to participation) minus (number of patients who voluntarily withdraw) divided by (number of subjects who were randomised)• AcceptabilityMeasure of the perception among study personnel and patients that the dHET is agreeable or satisfactory. Measured on a 5-point Likert scale for study personnel (where 5 is highly acceptable and 1 is poorly acceptable) and using the post intervention CSQ-8 survey for patients.▪ Adherence to protocolNumber of patients who completed their assigned intervention, also includes the proportion of complete data for each outcome measure (CSQ-8, STAI-6, REALM-R, demographic data collection)▪ Barriers to assigned interventionNumber of patients not randomised due to staffing or time constraints (with reason recorded), technology issues with tablet/dHET/link to knowledge quiz/internet access• TimeTime (minutes) taken to complete the assigned intervention (and any delays caused as a result)

Secondary outcomes:Knowledge recallNumber of answers correct in True/False/Unsure questionnaire, where a correct answer = 1 and incorrect/unsure = 0 (max score 20).Patient satisfactionMeasured using Client Satisfaction Questionnaire (CSQ-8) on the day of surgery and at 2-week follow-up phone call, a validated questionnaire to assess consumer satisfaction with health services. Scores range from 8 to 32, with higher values indicating higher satisfaction [30, 32, 33, 35].Patient anxietyMeasured at baseline, after the intervention and at the 2-week follow-up phone call, using the six-item State-Trait Anxiety Inventory (STAI-6), a short-form version of the state scale, consisting of six items chosen for reliability and validity, which produces scores that are comparable to using the full version [28].Delayed knowledge recall (at 2-week follow-up)Number of answers correct in True/False/Unsure questionnaire, where a correct answer = 1 and incorrect/unsure = 0 (max score 20).Time spent with surgeonTime (minutes) spent with surgeonNumber of questions asked by patientsNumber of questions patient asks after assigned intervention but before signing consent form

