## Trial progression

### Continuation criteria

Continuation criteria (Table 1) will be considered to determine whether further evaluation of this intervention is warranted (to test the effectiveness of the intervention) [41, 42]. These criteria are primarily based around the primary objective of feasibility and the potential for effectiveness and system-wide implementation.

**Table 1 Tab1:** Continuation criteria VVEIN pilot study

	**Proceed to RCT**	**Proceed to RCT following some changes to the protocol**	**Do not proceed to RCT unless problems can be overcome**
Recruitment	Recruitment of ≥ 80% study participants within 4 months	Recruitment of ≥ 60% study participants within 4 months [41]	Recruitment of < 60% study participants within 4 months
Retention	Retention of ≥ 80% of study participants for follow-up	Retention of ≥ 60% of study participants for follow-up	Retention of < 60% of study participants for follow-up
Feasibility and acceptability	dHET intervention on day ward acceptable to > 75% of study personnel (score of 4 or 5 on Likert scale) and patients involved (score of 28 or above on CSQ-8)	dHET intervention on day ward acceptable to > 50–74% of study personnel (score of 4 or 5 on Likert scale) and patients involved (score of 28 or above on CSQ-8)	dHET intervention on day ward acceptable to < 50% of study personnel (score of 4 or 5 on Likert scale) and patients involved (score of 28 or above on CSQ-8)
Non-adherence	Non-adherence to the intervention in < 10% (dHET and/or DOS questionnaires incomplete)	Non-adherence to the intervention in > 11–20% (dHET and/or DOS questionnaires incomplete)	Non-adherence to the intervention in > 21% (dHET and/or DOS questionnaires incomplete)

*dHET* Digital Health Education Tool, *DOS* Day of surgery

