### Subject withdrawal

Any participant can withdraw consent for participation at any point; they do no need to give a reason. Any participant wishing to withdraw can do so verbally or in writing to a member of the research team.

The investigator may withdraw a patient from the study if they:Experience a serious or intolerable adverse eventDevelops, during the course of the study, a condition which renders the patient unfit for interventionRequires early discontinuation for any reason

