### Trial closure

The trial shall be considered completed when a total of 40 participants have been randomised, as this will allow for up to 20% dropout rate.

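### The retention formula mixes consenters with randomised patients and subtracts only voluntary withdrawals, so it can exceed 100% and meet the proceed threshold when follow-up has failed

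*Protocol article*

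**What the plan says.** The section Data collection gives the article's only definition of the retention rate: "Number of patients who consent to participation) minus (number of patients who voluntarily withdraw) divided by (number of subjects who were randomised".

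The retention row of Table 1 (Continuation criteria) sets its top band at "Retention of ≥ 80% of study participants for follow-up" and its bottom band at "Retention of < 60% of study participants for follow-up".

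Consent has two stages (Study setting). In outpatients, "An initial consent and information process shall be carried out with patients deemed suitable for EVTA by their responsible surgeon". Later, on the day ward, "patients will be verbally reconsented for inclusion prior to randomisation and allocation to a study arm". Data collection also lists, as a primary outcome, the number of patients who are not randomised because staff or time were short, or because of technical problems.

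Subject withdrawal separates a participant's own withdrawal from withdrawal by the investigator: "The investigator may withdraw a patient from the study if they" meet any of three listed conditions. Follow-up is a telephone call at two weeks, when delayed knowledge recall is collected.

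On size, Trial closure says "The trial shall be considered completed when a total of 40 participants have been randomised", "as this will allow for up to 20% dropout rate".

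**The concern.** A retention rate should say what fraction of the randomised patients supplied follow-up data. This formula departs from that in two ways.

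- **Losses are left out.** Only voluntary withdrawal is subtracted. A patient who never answers the 2-week call, or whom the investigator withdraws, counts as retained.
- **Two populations are mixed.** The numerator starts from consenters and the denominator is the randomised. Every randomised patient has consented, so consenters cannot be fewer. A consenter who is not randomised for lack of staff or time has not withdrawn, and so adds to the numerator only.

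Retention is a primary outcome and one of four rows in the continuation table. The Discussion makes scale-up conditional on adequate recruitment and retention, and names knowledge recall as the future trial's primary outcome. Delayed recall is collected only at the 2-week call. A figure that ignores missed calls could therefore support a multicentre trial when the pilot had shown that 2-week data are hard to obtain.

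**Working it through.** The article states no computed retention figure to reproduce, so the check evaluates the formula directly. It is read with the subtraction done first.

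**Inputs from the protocol:** R = 40 randomised (Trial closure); cut-offs of 80% and 60% (Table 1).

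**Assumed inputs, because the protocol gives none:** C = consenters; W = voluntary withdrawals; I = withdrawn by the investigator; L = not reached at 2 weeks. In the table, all W are randomised patients who withdraw before the 2-week call.

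**Formulas**

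- Protocol: (C − W) / R
- Followed up among randomised: (R − W − I − L) / R

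**Consistency of the cut-off.** The dropout allowance in Trial closure gives 40 × (1 − 0.20) = 32, and 32/40 = 80%. This equals the top cut-off in Table 1, which suggests that the cut-off was meant for dropout among the randomised.

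**Results with R = 40**

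| C | W | I | L | Protocol formula | Followed up |
|---|---|---|---|---|---|
| 40 | 0 | 0 | 12 | 40/40 = 100%, proceed | 28/40 = 70%, proceed with changes |
| 40 | 0 | 0 | 18 | 40/40 = 100%, proceed | 22/40 = 55%, do not proceed |
| 40 | 8 | 0 | 9 | 32/40 = 80%, proceed | 23/40 = 57.5%, do not proceed |
| 40 | 2 | 2 | 16 | 38/40 = 95%, proceed | 20/40 = 50%, do not proceed |
| 50 | 16 | 0 | 0 | 34/40 = 85%, proceed | 24/40 = 60%, proceed with changes |
| 50 | 18 | 0 | 0 | 32/40 = 80%, proceed | 22/40 = 55%, do not proceed |
| 50 | 0 | 0 | 20 | 50/40 = 125%, proceed | 20/40 = 50%, do not proceed |

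The first four rows set C = R, so they show the omitted losses alone. Rows five and six have no silent losses and show the mixed populations alone. The last row combines both.

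**Direction of the error.** Let N be the consenters who are not randomised, and V the number of those N who count as voluntary withdrawals. Then C = R + N, and the total subtracted is W + V. The protocol figure minus the followed-up figure is

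(R + N − W − V)/R − (R − W − I − L)/R = (N − V + I + L)/R.

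V cannot exceed N, so no part of this is negative: the formula is either right or too high. It exceeds 100% whenever N − V is greater than W.

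**Other rows of Table 1.** The non-adherence row covers the digital tool and the day-of-surgery questionnaires. The recruitment and acceptability rows do not measure follow-up. No row would catch 2-week loss.

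**The case against.** The strongest reply concerns the meaning of consent. Patients are re-consented on the day of surgery, and the envelope is drawn once that consent is confirmed. If the formula means this second consent, C is about equal to R and the excess over 100% largely disappears. Some patients are still unsure when they leave outpatients, which gives this reading some support. Likewise, a patient who declines at re-consent could be counted as a voluntary withdrawal. If all 10 non-randomised patients in the 50-consenter cases did so, the fifth row would give (50 − 26)/40 = 60%, equal to the followed-up figure, and the last row (50 − 10)/40 = 100% rather than 125%.

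This stands as a limit on the second fault: its size depends on how consent is read and on why patients were not randomised. It does not remove that fault, because the protocol itself expects some patients to go unrandomised for reasons that are not withdrawal. It does not touch the first fault: even in the softened last row, the formula reads 100% against 50% followed up.

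A second reply is that Table 1 does not cite the formula, that its plain wording points to follow-up, and that the criteria are to be considered rather than applied mechanically. The wording does suggest that the proportion followed up was intended. But no other definition of retention is given, so one term covers two different quantities and the two sections must be reconciled.

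A third reply is that loss would be visible elsewhere, in the outcome reporting completeness of data and in the CONSORT flow diagram. That is fair as regards visibility. Yet the completeness list does not name the knowledge questionnaire, and none of it feeds a continuation criterion for the 2-week call.

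**Conclusion.** The definition is wrong as written and needs to be changed. On any reading of consent, missed 2-week calls and investigator withdrawals do not lower the rate. With C = R = 40 and no withdrawals it stays at 100% however many patients are not reached: 12 not reached is truly 70%, and 18 is truly 55%. That is enough to move the result by one or two bands of Table 1.

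If consent means the outpatient consent, each consenter who is not randomised and not counted as a withdrawal adds a further 1/40 = 2.5 percentage points, and the figure can pass 100%. The 50-consenter cases rest on an assumed count and on none of the extra 10 being classed as voluntary withdrawals.

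The error never runs downward, so it can only favour proceeding.

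**What to change.** Replace the definition in Data collection with: randomised participants who complete the 2-week call, including the delayed knowledge questionnaire, divided by all randomised participants. State that non-contact and withdrawal of either kind count as not retained, and have the retention row of Table 1 refer to this definition. Report attrition before randomisation separately, as randomised divided by consented, and say which consent is meant.

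Two additions would help but are not essential: showing retention by arm, and stating whether 2-week data are still sought from patients whom the investigator withdraws and who do not refuse. The second is a procedural point and would have to fit with Subject withdrawal.

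The core change is one reworded definition and a cross-reference. It uses data from a call already planned and needs no more patients. Its only cost is that the reported retention may be less favourable.
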